### Study design

This study will examine the effects of emotion recognition training on a sample of individuals with depressive symptoms over a 6-week follow-up period. Participants will attend a screening session and will be randomised to intervention or control procedures, repeated five times over consecutive days (Monday to Friday). A follow-up session will take place at end-of-treatment, 2-weeks and 6-weeks after training.

### Primary outcome measures

The primary outcome measure is depressive symptoms, using the BDI-II (rated over the past 2 weeks).

### Secondary outcome measures

The secondary outcome measures are: depressive symptoms, using the Hamilton Rating Scale for Depression; anxiety symptoms, using the Beck Anxiety Inventory (rated over the past month); positive affect, using the PANAS (rated as ‘how you feel right now’); negative affect, using the PANAS (rated as ‘how you feel right now’); emotion sensitivity, using the Emotion Recognition Task (test phase); approach motivation and persistence, using the Fishing Game; and depressive interpretation bias, using the Scrambled Sentences Test.

### Procedures

We will recruit 190 adults from the general population who report depressive symptoms (defined as a score ≥ 14 on the BDI-II). Approximate timings of the screening day procedures are presented in Table 1. Participants will provide informed consent and inclusion/exclusion criteria will be assessed. Screening will consist of structured clinical interview for Diagnostic and Statistical Manual of Mental Disorders, fourth edition, using the Clinical Interview Schedule [13], the Altman Self-Rating Mania Scale (for bipolar disorder) [14], and medical history. After initial screening we will collect baseline data on age, sex, ethnicity, alcohol, tobacco and caffeine use, previous history of depression (treated and non-treated), intelligence (National Adult Reading Test) [15], number of years of education, social network size, and current and past history of psychiatric treatment. At screening we also will assess whether participants meet criteria for clinical depression, number of episodes of depression, age at first episode, and whether participants have ever taken antidepressant medication (including details of how recently).

**Table 1 T1:** Timings of procedures of screening session (day 1)

**Time (minutes post arrival)**	**Task**
0	Informed consent
15	Screening
40	Baseline measures
50	Mood assessments
60	Computerised training
90	Depart

Participants will be randomised to intervention; a training procedure designed to promote the perception of happiness over sadness in ambiguous emotional expressions, or a control procedure designed to elicit no change in perception of emotional expression (described below). Participants will complete computerised training (or control) procedures repeated five times over consecutive days (Monday to Friday). Each session will consist of three phases: baseline, training, and test. Approximate timings of the treatment-day procedures are presented in Table 2.

**Table 2 T2:** Timings of procedures of treatment sessions (days 2 to 5)

**Time (minutes post arrival)**	**Task**
0	Computerised training
20	Depart

Mood assessments (BDI-II, Beck Anxiety Inventory, Hamilton Rating Scale for Depression and PANAS) will be taken at baseline, at the end of treatment, and at 2-week and 6-week follow-up. Behavioural assessments (Emotion Recognition Task, Scrambled Sentences Test, and the Fishing Game) will be taken at the end of treatment, and at 2-week and 6-week follow-up. 6-week follow-up will also include a visual analogue scale rating of how helpful the participant thought the experimenter was, to ensure that there are no differences between treatment groups which may affect blinding. At 6-week follow-up will we reassess the initial exclusion criteria, to establish any change in these (Table 3).

**Table 3 T3:** Timings of procedures of follow-up sessions (end of treatment, 2 weeks and 6 weeks)

**Time (minutes post arrival)**	**Task**
0	Mood assessments and behavioural tasks
20	Exclusion criteria (6-week only)
30	Visual analogue scale rating of experimenter (6-week only)
40	Depart

### Measures and materials

#### Training task

The baseline and test phases each consist of 45 trials, in which each of the stimuli from the morph sequence is presented to the participant three times. The task requires the participant to make a forced choice judgement as to whether the presented face is displaying a sad or happy expression. Images are presented one at a time, in random order, for 150 milliseconds. Stimuli are preceded by a fixation cross, which is presented for a random period ranging from 1500 to 2500 milliseconds. Subsequent to presentation, and to prevent processing of afterimages, a backward mask of noise is presented for 250 milliseconds, followed by a prompt asking the participant to respond. This remains on screen until the participant makes response (i.e., a judgement of ‘sad or ‘happy).

Each trial in the training phase is similar to a trial in the baseline and test phases with respect to inter-trial interval and stimuli presentation, but with the addition of feedback subsequent to the participant’s response. In the control condition, feedback is based on the participant’s baseline balance point. That is, responses are classified as ‘correct’ if the participant identified images below the original balance point image as ‘sad’ and above it as ‘happy’, and otherwise are classified as ‘incorrect’. Feedback is a message saying ‘Correct / Incorrect! that face was sad/happy’. In the training condition, feedback is again based on the participant’s baseline balance point, but the ‘correct’ classification is shifted two morph steps towards the ‘sad’ end of the continuum, so that the two images nearest the balance point that the participant would previously have classified as ‘sad’ at baseline are considered ‘happy’ when providing feedback. In each training block, each face from the 15 face continuum is presented twice. The order of presentation is randomised within each block. Six training blocks are given to each participant, resulting in 180 training trials in total.

Prototypical ‘sad’ and ‘happy’ composite images have been generated from 20 individual male faces showing a sad facial expression, and the same 20 individuals showing a happy expression. Original images come from the Karolinska directed emotional face set [16]. To construct these images, the 40 original images were each delineated with 172 feature points, which allows both shape and colour information to be averaged across the faces to generate ‘average’ sad and happy expressions, using established techniques [17]. These prototypical images were used as endpoints to generate a linear morph sequence that consists of images that change incrementally from unambiguously ‘sad’ to unambiguously ‘happy’, with emotionally ambiguous images in the middle. We have created a sequence with 15 equally spaced images for use as experimental stimuli (see Figure 1 for endpoints and example intermediate stimuli).

#### Approach motivation and persistence: the fishing Game

In this task, 12 brightly coloured plastic fish move round in a circle, opening and closing their mouths to reveal a magnet [18]. Participants are required to catch as many fish as they can in 2.5 minutes by ‘hooking’ them using a magnet on the end of a 900 mm plastic fishing rod. The fishing game task is a simple behavioural performance measure assumed to tap behaviour negatively associated with dysphoria, such as approach motivation and persistence.

#### Depressive interpretation bias: scrambled sentences test

In this task, participants unscramble a list of 20 scrambled sentences (e.g., ‘winner born I am loser a’) under a cognitive load (remembering a six-digit number) [19]. This task measures the tendency of participants to interpret ambiguous information either positively (‘I am a born winner’) or negatively (‘I am a born loser’). A negativity score is generated by calculating the proportion of sentences completed correctly with a negative emotional valence.

#### Social network size: friendship and social network size

In this task, participants rate the number of close friends they currently have on a 5-point scale ranging from 0 (none) to 4 (four or more) [20]. A close friend is defined as a person whom respondents report feeling close to and whom they believe they could confide in and turn to for help. Participants will also repeat this process, rating the number of contacts and acquaintances they currently have. A contact or acquaintance is defined as a person known by sight or known to someone, but not intimately.

### Statistical plan

We will use linear regression to evaluate the effect of training on mood at 6-week follow-up. Analyses will be adjusted for age, sex, ethnicity, previous history of treatment for depression, and baseline mood. The primary outcome will be depressive symptoms assessed using the BDI-II. Secondary outcomes will include depressive symptoms measured using the Hamilton Rating Scale for Depression, and positive and negative affect assessed using the PANAS.

Subgroup analyses by whether participants meet criteria for clinical depression, number of episodes of depression, age at first episode, and whether participants have depression with or without anxiety will also be conducted. We will also analyse the impact of social network size on treatment effect. We predict that larger social network will be associated with an enhanced treatment effect.

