### Study objectives and hypotheses

The present project aims to establish the effects of emotion recognition training on mood in a sample of individuals with depressive symptoms over a 6-week follow-up period. Preliminary evidence suggests a beneficial effect of emotion recognition training on positive mood at 2-week follow-up following four consecutive days of training [10]. However, we would hypothesise that these effects would strengthen over time, by modifying the nature of social interaction through the perception of positive emotion over negative emotion. We will therefore investigate the longer-term effects of training over time, using a 6-week follow-up period. We hypothesise that individuals randomised to receive an intervention designed to modify emotion perception designed to increase the perception of happiness over sadness in ambiguous expressions will show reduced depressive symptoms, reduced negative affect, and increased positive effect, compared with individuals randomised to receive a placebo intervention.

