### Sample size determination

Our preliminary data indicate an effect size of *d* = 0.43 at 2-week follow-up, corresponding to a difference of 3 points on the Positive and Negative Affect Schedule (PANAS). This indicates that a sample size of *n* = 172 will be required to achieve 80% power at an alpha level of 5%. This effect size may be conservative as our data indicate a trend for the effect of training to strengthen over time, which is consistent with our underlying theoretical model. This sample size will give us equivalent power to detect a difference of 5 points on the BDI-II. We will therefore recruit *n* = 190 participants, including 10% over-recruitment to accommodate potential attrition.

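### The planned 6-week regression validly compares the groups but cannot test the stated hypothesis that effects strengthen over time, and as written it gives earlier scores no role when week 6 is missing

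*Protocol article*

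**What the plan says.** All references are to the protocol article.

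- **Analysis.** The Statistical plan states "We will use linear regression to evaluate the effect of training on mood at 6-week follow-up". It continues: "Analyses will be adjusted for age, sex, ethnicity, previous history of treatment for depression, and baseline mood". It names the BDI-II as primary: "The primary outcome will be depressive symptoms assessed using the BDI-II". The section adds subgroup analyses and an analysis of social network size, but no comparison of effects between visits.
- **Data.** Under Procedures, the mood scales (BDI-II, Beck Anxiety Inventory, Hamilton scale, PANAS) "will be taken at baseline, at the end of treatment, and at 2-week and 6-week follow-up". That gives three post-training scores per person.
- **Time course.** Study objectives and hypotheses reports a pilot benefit on positive mood at 2 weeks and goes on: "However, we would hypothesise that these effects would strengthen over time". The aim follows: "We will therefore investigate the longer-term effects of training over time, using a 6-week follow-up period". The same section ends with a between-group hypothesis: fewer depressive symptoms, less negative affect and more positive affect than under placebo.
- **Attrition.** Sample size determination meets expected losses by recruiting 190 where 172 are needed.

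**The concern.** The protocol states a hypothesis about how the effect changes between visits and collects the data to examine it, but the only treatment-effect analysis it names has one outcome visit. One treatment coefficient at 6 weeks fits a growing, a stable or a fading effect equally well, whatever the sample size. The trial could end with a clear 6-week result and no pre-specified answer on strengthening, which the protocol links to its proposed mechanism.

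The second part concerns dropout. In the regression as written, someone with end-of-treatment and 2-week scores but no 6-week score does not enter. Over-recruitment replaces the lost numbers; it does not remove bias if people with worse 2-week mood are more likely to miss week 6. Where training works, controls score higher at 2 weeks, so more high scorers would be lost from the control arm. The 6-week difference would then shrink towards zero.

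**Working it through.** **1. The plan's own figure.** Inputs from Sample size determination: d = 0.43, 80% power, alpha 5% (two-sided assumed). The two-sample t-test needs 85.87, so 86 per arm and 172 in total, as stated. 172 × 1.10 = 189.2, hence 190. Planned loss: 18/190 = 9.5%. The arithmetic fits an analysis of about 172 people with a 6-week score.

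**2. Hypothesis against model.** Strengthening means that (treatment effect at 6 weeks) minus (treatment effect at 2 weeks) differs from zero. The stated model estimates only the first term, and none of its covariates is a post-training score. The difference therefore cannot be estimated from it.

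**3. Attenuation under score-dependent dropout.** The documents give no dropout mechanism, residual SD or within-person correlation, so these are assumptions: true effect -5 at both visits, residual SD 9.5, 2-to-6-week residual correlation 0.5 or 0.7, baseline SD 7 with slope 0.6. Log-odds of missing week 6 rise by a fixed slope per 2-week BDI-II point. I simulated 4 million participants per cell and fitted the baseline-adjusted regression to those with a 6-week score:

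| Correlation | Slope | 9.5% missing | 20% missing |
|---|---|---|---|
| 0.5 | 0.03 | -4.99 (0.2%) | -4.95 (0.9%) |
| 0.5 | 0.05 | -4.97 (0.6%) | -4.92 (1.6%) |
| 0.5 | 0.10 | -4.85 (2.9%) | -4.76 (4.8%) |
| 0.5 | 0.15 | -4.76 (4.9%) | -4.59 (8.1%) |
| 0.7 | 0.03 | -4.98 (0.4%) | -4.95 (1.0%) |
| 0.7 | 0.05 | -4.94 (1.1%) | -4.88 (2.4%) |
| 0.7 | 0.10 | -4.79 (4.2%) | -4.65 (6.9%) |
| 0.7 | 0.15 | -4.66 (6.9%) | -4.41 (11.8%) |

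Percentages are attenuation. A likelihood estimate that also uses the 2-week score returned -4.98 to -5.01 in every cell shown. Slopes of 0.10 and 0.15 are strong: the odds of dropout rise by exp(0.10 × 9.5) = 2.6 and exp(0.15 × 9.5) = 4.2 per 9.5-point SD. For scale, the standard error with 172 analysed is about 9.5 × √(4/172) = 1.45 points. The bias at planned attrition with these slopes is about 0.15 to 0.35 points.

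**4. Precision.** If the earlier scores explain a share R² of 6-week variance given baseline, and a fraction d is lost, a repeated-measures model gains a factor 1/(1 − R²d) in effective numbers. With assumed visit correlations of 0.3 to 0.7 (compound-symmetric or AR(1)), R² runs from 0.09 to 0.42. At d = 0.095 this gives 172 × 1.008 ≈ 173 up to 172 × 1.042 ≈ 179, or power of 80.8% to 82.1% against 80.5%.

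**5. Power of a strengthening test.** With 86 per arm, in SD units, the change score has SD √(2(1 − ρ)) and the contrast has standard error √(2(1 − ρ)) × √(2/86). For an increase of 0.2 SD:
- ρ = 0.3: 0.2/0.180 = 1.11, power 20%.
- ρ = 0.7: 0.2/0.118 = 1.69, power 40%.

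For an increase of 0.43 SD, power is 66% to 95%.

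**The case against.** Baseline-adjusted regression at one visit is a standard primary analysis. The randomised comparison that closes Study objectives and hypotheses is between groups, and the 6-week regression tests it directly. A reader might infer that the primary analysis is invalid, or that the trial's central hypothesis goes untested. The protocol supports neither. The strengthening sentence is a further hypothesis, it follows a statement about positive mood rather than the BDI-II, and it also serves as the reason for a 6-week endpoint.

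A reader might also infer that the plan commits to discarding dropouts' earlier scores. It does not say so. The article is silent on missing data, linear regression is compatible with imputation from earlier visits, and such detail commonly sits in an SAP, which is not shown. The dropout part is therefore conditional.

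The size of the bias rests on invented dropout slopes. With weak dependence it is negligible, it runs towards no effect, and with no true effect the estimate is unbiased, so false positives are not the worry. The precision gain is slight. The end-of-treatment BDI-II, rated over the past 2 weeks after five days of training, partly covers the time before training and says little about growth.

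All of this stands as a limit on size. It does not remove the mismatch: the Statistical plan finds room for subgroups and social network size, but gives no analysis to a time-course hypothesis that the protocol states in its own words.

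**Conclusion.** The point holds in a limited form. The 6-week regression is a valid test of the between-group hypothesis, but the strengthening hypothesis has no named test although the data for one are collected. That part needs no outside assumption.

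The dropout part applies only if missing 6-week scores are not imputed elsewhere from earlier visits and if dropout depends on 2-week mood. Under the assumed effect of -5, residual SD 9.5 and correlation 0.5 to 0.7, attenuation is about 0 to 2% for weak dependence. At the planned attrition with stronger dependence it is 3 to 5% (correlation 0.5) or 4 to 7% (correlation 0.7). It reaches 11 to 12% only at 20% loss, the steepest slope and correlation 0.7. This is a modest, avoidable bias. The change is worth making for the untested hypothesis and the bias, not for power.

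**What to change.** Fit one linear mixed repeated-measures model to all post-training scores, with treatment, visit, treatment-by-visit, baseline-by-visit, the covariates already listed and an unstructured covariance. Keep the 6-week BDI-II treatment contrast as primary. Pre-specify the 6-week minus 2-week treatment contrast as a secondary test of strengthening, for PANAS positive affect as well as the BDI-II. Use the same model for the other mood scales.

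The cost is a change of analysis wording and a slightly more complex model. With complete data the 6-week estimate is essentially that of the planned regression. Trial status reports one participant recruited at submission, so at that stage the change could be fixed without knowledge of outcomes. The plan should acknowledge that the strengthening test has low power for small increases, and that the end-of-treatment BDI-II overlaps the pre-training period. The model remains valid only if dropout is explained by observed scores and covariates.

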## Discussion

Here we propose a study to investigate the potential of a novel cognitive bias modification technique for reducing negative mood and improving positive mood in an analogue population of those with high levels of depression symptoms. This targets biases in emotional processing characteristic of depression, and can be delivered automatically via computer, Internet or Smartphone. This technique therefore has potential to be a valuable cost-effective adjunctive treatment for depression which may be used together with more traditional psychotherapy, CBT and pharmacotherapy.

Our approach is to model treatment development in analogue populations before development in the disorder of interest. In this case our analogue groups are people suffering from depressive symptoms (dysphoria) but are not selected on the basis of a clinical diagnosis. This approach allows us to refine the ingredients of successful intervention and to establish the best clinical study to subsequently carry out in a depressed cohort. In particular, it avoids potential confounding effects of medication, and allows fast recruitment of a group characterised by negative emotion processing biases. The approach is a well-validated method in the wider basic psychology literature, and provides a useful model of depression to explore treatment effects before translation into a full clinical trial.

## Trial status

This article was submitted on 19 September 2012. To date, one participant has been recruited. The first participant was enrolled on 3 September 2012.

## Abbreviations

BDI-II: Beck depression inventory II; CBT: Cognitive-behavioural therapy; PANAS: Positive and negative affect schedule.
